| Staged Procedures         | Subjects may undergo staged surgical procedures prior to device activation, as determined by local standards of care.                                                                                                                                                                                                                                                                                                                                                                                                                                                                                                                                                                                                                                                                                                                                                                           |                                 |      |                                  |      |
| Statistical Methods       |                                                                                                                                                                                                                                                                                                                                                                                                                                                                                                                                                                                                                                                                                                                                                                                                                                                                                                 |                                 |      |                                  |      |

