### **11.6. *Implant Procedure(s) of Vercise System***

Detailed directions for use will be available to each investigator and investigational site in the form of instructional manuals and training by BSC staff. Because DBS is a well-established therapy, neurosurgeons, neurologists, and their staffs have developed their own best procedures and practices for implant, activation, and programming. Standard practices, per local DFUs will be followed for the placement of the Vercise system.

The date of the first lead placement will be considered as Day 0. Alternatively, for subjects receiving BSC IPG and BSC Pocket adaptor as a replacement to non-BSC IPG, the day of BSC IPG implant will be considered as Day 0. Also, if newly marked CE active components- such as the lead or IPG are used, then that day shall be considered as Day 0. All subsequent study schedule visits will occur based on the timing of the Day 0 visit.

Standard practices, per local DFUs will be followed for the placement of the Vercise system.

Post-operative imaging is recommended to be done within 3 months following placement of leads to confirm lead position. A computerized tomography (CT scan) with at least 1.25 mm slice thickness is recommended.

The implant procedure must be performed within 6 months of the baseline.

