## **14. Study Assessments**

### **14.1. *Adverse Events***

Adverse event evaluation will be conducted to identify adverse events occurring during the study and to classify them with regards to seriousness, severity, and relationship to either study procedure and/or study-device action. Additionally, an assessment of actions taken to address adverse events and their outcome will be conducted. Safety events will be reported as specified in Table 20-3. Only non-serious adverse events that are related to the device, stimulation, or procedure, and serious adverse events will be recorded. SAEs and USADEs will be collected from the time of informed consent through the end of the study.

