### **19.3. *Anticipated Adverse Events***

The following anticipated adverse events (AE) have been identified for this study. These include risks that could occur due to the implant procedure, revision of system, explant, or replacement of device:

- Allergic, immune system response or reaction;
- Anesthesia/neurosurgery risks, including unsuccessful implant, exposure to blood borne pathogens;
- CSF leak;
- Death, including suicide;
- Embolism, including air embolism and pulmonary embolism;
- Hemorrhagic or ischemic stroke, immediate or delayed, which could result in temporary or permanent neurologic deficits such as muscle weakness, paralysis or aphasia;
- Implant site complications such as pain, poor healing, wound reopening;
- Infection;
- Injury to tissues adjacent to implant or within surgical field, such as blood vessels, peripheral nerves, brain (including pneumocephalus), or pleura (including pneumothorax);
- Cognitive impairment such as attention or executive deficits, memory disturbances, confusion, or dysphasia;
- Psychiatric disturbances such as anxiety, depression, apathy, mania, insomnia, suicide, or suicidal ideation or attempts;
- Motor problems such as paresis, weakness, incoordination, restlessness, muscle spasms, postural and gait disorders, tremor, worsened dystonia, or dyskinesias, and falls or injuries resulting from these problems;
- Musculoskeletal stiffness;
- Pain, headache or discomfort, transient or persistent;
- Poor initial lead location, which may lead to ineffective therapy, side effects, or a surgical revision;

- Radiation exposure due to imaging (CT, fluoroscopy x-ray);
- Seizures;
- Sensory changes (e.g. changes in hearing, taste, or other senses);
- Seroma, edema or hematoma;
- Speech or swallowing problems such as dysarthria or dysphagia, as well as complications of dysphagia such as aspiration pneumonia;
- Symptoms in other systems, such as tachycardia, sweating, fever, dizziness, changes in renal function, urinary retention, sexual effects, nausea, bowel retention, bloating;
- Thrombosis;
- Visual disturbances or periorbital symptoms, such as diplopia, eyelid movement difficulty, oculomotor difficulties or other visual field effects.

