**Table 20.2-1: Adverse Event Definitions**

| Term                                                                                     | Definition                                                                                                                                                                                                                                                                                                                                                                                                                                                                                                                                                                                                           |
|------------------------------------------------------------------------------------------|----------------------------------------------------------------------------------------------------------------------------------------------------------------------------------------------------------------------------------------------------------------------------------------------------------------------------------------------------------------------------------------------------------------------------------------------------------------------------------------------------------------------------------------------------------------------------------------------------------------------|
| Adverse Event (AE)

Ref: ISO 14155

Ref: MEDDEV 2.7/3          | Any untoward medical occurrence, unintended disease or injury, or any untoward clinical signs (including an abnormal laboratory finding) in subjects, users or other persons, whether or not related to the investigational medical device.

NOTE 1: This includes events related to the investigational medical device or comparator.

NOTE 2: This definition includes events related to the procedures involved (any procedure in the clinical investigation plan).

NOTE 3: For users or other persons, this definition is restricted to events related to the investigational medical device. |

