**NOTES:**

- For the purposes of this study, hospitalization is defined as any in-patient admission.
- Hospitalizations occurring for the purpose of performing a planned procedure as per routine/standard of care such as programming sessions or standard evaluation, staged implant procedures or rehabilitation are NOT to be reported as a SAE.
- Any complications or adverse events that occur during an elective/planned hospitalization, should be reported if they meet the protocol specified definitions. However, the original elective/planned hospitalization(s) should not be reported as an SAE.
- Sensations or side effects that occur during programming should not be reported as AEs. However, persistent unpleasant sensations or side effects that occur after the completion of programming will be reported.
- Ineffective therapy (e.g. lack of efficacy, lack or decrease of therapeutic response) will not be collected as an adverse event, since failure to achieve therapeutic response is an issue of efficacy, not safety. No AE of “Ineffective Therapy” should be reported when using the expanded parameter range for purposes of improving ineffective therapy. However, AEs due to sudden loss of efficacy (e.g. loss of stimulation leading to a fall or injury) will be collected.
- The subject’s dystonia symptoms will not be collected as AEs, unless they have worsened beyond baseline and beyond the expected disease progression over time. This worsening event could occur in the context of a device malfunction or with a properly-functioning device as determined by investigator).

- Device migration will not be collected as an adverse event. However, an AE that results from the device/lead migration should be reported as an AE. Device migration should be reported as a device deficiency in the electronic database.
- In the case of death, efforts should be made to perform an autopsy. If an autopsy is performed the study device should be explanted and returned to BSC. If no autopsy is performed, attempt should be made to explant the device, if feasible, and the device returned to BSC. As well, the device should be explanted before cremation due to risk of battery explosion when exposed to extreme heat. A copy of the death records and an autopsy report (if available) should also be sent to Boston Scientific as soon as possible, provided that such activities do not violate patient consent and patient data confidentiality.

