|                                                                                                                                                                                                                                                                                                                                                                         | sponsor                                                                                                                                                    |                                                                                                                                                                                                                                                                                                                           |
| Serious Adverse Device Effects**                                                                                                                                                                                                                                                                                                                                        | Complete AE eCRF page with all available new and updated information

Provide all relevant source documentation (unidentified) for reported event    | 
 
• Within 2 business days of first becoming aware of the event or as per local/regional regulations.
 
• Reporting required through the end of the study for all events related to hardware, stimulation and procedure
 
• When documentation is available
 
 |

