  - **Procedure Related AEs:** AEs that can reasonably (i.e. Unlikely, Possibly, Probably and Causally Related) be attributed to a study protocol required procedure.

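### Section 20.4 counts only procedures the protocol requires, so complications of revision, repositioning, replacement or explant can fall outside the recorded or device-related events

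*Protocol*

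**What the plan says.** Section 14.1 sets the filter for what enters the database: "Only non-serious adverse events that are related to the device, stimulation, or procedure, and serious adverse events will be recorded". A footnote to Table 11-1 repeats it.

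Section 20.4 then gives three categories of relatedness: device hardware, stimulation and procedure. The third covers events that can reasonably be "attributed to a study protocol required procedure". A footnote to Table 20.4-1 extends ADEs, SADEs and USADEs to events in any of the three categories.

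Other sections describe procedures more broadly:
- Table 20.2-1, in a note to the adverse event definition: "This definition includes events related to the procedures involved (any procedure in the clinical investigation plan").
- Section 19.3, on the anticipated adverse events: "These include risks that could occur due to the implant procedure, revision of system, explant, or replacement of device".
- Section 20.1 asks for all events related to a study procedure and does not define the term.

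Section 11.13 says leads or the IPG may need repositioning, replacement or explant, and asks that such operations be documented. Section 7 lists as safety parameters the rates of SAEs and of ADEs, including SADEs and USADEs, at 3 years after first lead placement.

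**The concern.** Relatedness to a procedure does two jobs here. For a non-serious event it helps decide whether the event is recorded at all. For a serious event it helps decide whether the event is classed as a SADE and which reporting deadline applies. If the operative definition is narrower than the set of operations the protocol expects, sites can exclude complications of the unlisted operations while following the text exactly.

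The registry may run at up to 40 sites, each of which can read the word required in its own way. Events that never reach the database cannot be recovered by any analysis plan. For the affected events the error runs one way, towards lower ADE and SADE rates.

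**Working it through.** There is no stated figure to reproduce. The check is a comparison of texts, with one subtraction of deadlines.

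**1. Scope of procedure in each place**

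| Place | Scope | Reaches revision, repositioning, replacement, explant? |
|---|---|---|
| 20.4, procedure-related category | Procedures the protocol requires | Not named; no on a literal reading |
| Table 20.2-1, adverse event, note 2 | Any procedure in the plan | Yes, since 11.13 is part of the plan |
| Table 20.2-1, ADE, note 1 | Includes implantation | Not named; replacement arguably, as a new component is implanted |
| 19.1 | Device effects during a study surgical procedure | Term undefined |
| 19.3 | Implant, revision, explant, replacement | Yes; repositioning only as a form of revision |
| 20.1 | Study procedure | Term undefined |

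**2. Are re-operations required?** Section 11.13 presents them as responses to misplacement, migration, failure, infection or discomfort. Nothing in the protocol mandates them. The initial implant differs: section 11.6 says it must take place within 6 months of baseline.

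**3. Non-serious event.** Take an anaesthesia complication at an elective repositioning of the IPG, and test it against the three categories of 20.4.
- Hardware: it does not come from the presence of the device or from a deficiency of it.
- Stimulation: it does not come from stimulation.
- Procedure: the operation was not required by the protocol.

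On that reading it fits no category, and section 14.1 does not call for it to be recorded. Under the wider scope it would be an ADE, with entry recommended within 30 business days.

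**4. Serious event of the same kind.** Section 20.4 collects SAEs whatever their relationship, so the event is recorded. Only its class and deadline change (Table 20.4-1):
- Counted as procedure-related, it is a SADE: "Within 2 business days of first becoming aware of the event or as per local/regional regulations".
- Not counted as related, it is an SAE: 10 business days, or as local rules require.
- Difference: 10 − 2 = 8 business days.
- Austria: the SAE limit is also 2 business days, so 2 − 2 = 0.

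**5. Effect on the safety parameters.** The SAE rate is unaffected. The ADE rate can lose non-serious and serious re-operation events, and the SADE rate can lose the serious ones. The protocol gives neither a re-operation rate nor a complication rate per re-operation, so the size of the loss cannot be computed.

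**6. Staged implant.** The synopsis says: "Subjects may undergo staged surgical procedures prior to device activation, as determined by local standards of care". The notes after Table 20.2-1 place among routine care a hospital stay for a "planned procedure as per routine/standard of care such as programming sessions or standard evaluation, staged implant procedures or rehabilitation". These lines cast some doubt on whether each stage is a required procedure, but they do not exclude it.

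**The case against.** The case against has several strong parts.

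- **Initial implant.** A reader might infer that implant complications are also lost, because "Standard practices, per local DFUs will be followed for the placement of the Vercise system". The documents do not support that. Local practice governs technique and staging, but the implant is a scheduled, mandatory step and implantation is inside the ADE definition. The notes exempt the planned admission itself, not complications during it.
- **Serious events.** A reader might infer that serious surgical harm goes unrecorded. It does not, because SAEs are reported regardless of relationship.
- **Typical surgical complications.** A reader might infer that a CSF leak or haemorrhage at lead revision is unrelated by definition. Section 19.1 lists both among the anticipated device effects, and Table 20.3-1 grades relatedness on known side effects of similar devices and procedures, timing and body site. Many such events would be classed as related.
- **Device-driven re-operations.** Where migration or failure prompts the operation, an investigator may attribute the complication to the device deficiency.
- **Backstops.** Section 20.1 asks for submission when it is unclear whether an event fits a category, and section 20.4 counts even an unlikely relationship as attributable.

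The first three points stand and limit the finding. The fourth narrows it case by case. The backstops do not close the gap. The provision in 20.1 relies on the same undefined word, and a site reading 20.4 literally may see nothing unclear. Counting unlikely relationships widens the degree of causality but not the list of qualifying procedures. The notes require complications of planned admissions to be reported only if they meet the protocol's definitions, which leads back to 20.4.

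It may also be said that the note in Table 20.2-1 defines an adverse event while 20.4 sorts events already so defined. That is fair, but with recording tied to relatedness, the sorting decides what is captured.

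**Conclusion.** The concern holds in a limited form. The protocol uses inconsistent scopes of procedure, and the narrowest is the one that decides relatedness. The exposed events are complications of revision, repositioning, replacement or explant that are due to the surgery or anaesthesia and not to hardware or stimulation. Non-serious ones can go unrecorded. Serious ones can lose the SADE label and be due 8 business days later, with no difference in Austria and possibly less elsewhere under local rules.

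This assumes a site applies 20.4 literally and does not use the provision in 20.1. The direction of any bias in the 3-year ADE and SADE rates is downward, but its size is unknown. Applying an assumed re-operation rate to the 200 subjects would not help: the documents supply no such rate, and the result would count operations rather than complications. Nor do they support saying that all non-serious re-operation events are lost, since sites may read the text more broadly. The gap still warrants a wording change because the lost data could not be recovered later.

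**What to change.** Reconcile the passages by stating one scope of procedure and using it in sections 14.1, 20.1, Table 20.2-1 and 20.4. It should explicitly include:
- every stage of the implant;
- revision, repositioning, replacement and explant of any system component;
- the anaesthesia associated with any of these;
- assessments that the study requires.

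The Table 11-1 footnote and the case report form guidelines should follow the same wording. This would also settle the staged-implant ambiguity.

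The change is one definition, with no new visits and no effect on how subjects are treated. The downside is a slightly higher reported ADE and SADE rate and slightly more reporting work for sites.

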### **20.5. *Boston Scientific Device Deficiencies***

All device deficiencies (including but not limited to failures, malfunctions, use errors, product nonconformities, and labeling errors) will be documented and reported to BSC. If possible, the device(s) should be returned to BSC for analysis. Instructions for returning the investigational device(s) will be provided. If it is not possible to return the device, the investigator should document why the device was not returned and the final disposition of the device. Device failures and malfunctions should also be documented in the subject's medical record.

All device deficiencies whether or not associated with an adverse event should be reported on the device deficiency eCRF.

Device deficiencies (including but not limited to failures, malfunctions, and product nonconformities) are not to be reported as adverse events. However, if an adverse event is associated with a device deficiency, that specific event should be recorded in the AE eCRF.

If a device deficiency could have led to a serious adverse event if A) suitable action had not been taken or B) intervention had not been made or C) if circumstances had been less fortunate is considered a reportable event.

### **20.6. *Reporting to Regulatory Authorities / ECs / Investigators***

BSC is responsible for reporting adverse event information to all participating investigators and regulatory authorities, as applicable.

The Sponsor, Investigator, or Site must notify the IEC of any USADEs, SADEs, SAEs, and other events as applicable according to local reporting requirements. A copy of the Investigator's reports and other relevant reports (if applicable) to the IEC must be provided to BSC in accordance with the local requirements.

Boston Scientific Corporation will notify all participating study centers if SAEs/SADEs occur which imply a possible increase in the anticipated risk of the procedure or use of the device or if the occurrence of certain SAEs/SADEs demands changes to the protocol or the conduct of the study in order to further minimize the unanticipated risks.

